### 6.2 Exclusion criteria

If any of the following criteria apply, patients cannot be included in the trial:

- Patient has an implanted cardiac pacemaker
- Patient has epilepsy
- Patient has spinal cord pathology
- Is pregnant or breastfeeding

### 6.3 Participant recruitment

Eligible patients will be identified through MDT meetings and screening of patients medical notes by members of the research team who will be the clinicians normally providing their routine clinical care.

Patients' usual clinicians will be asked to offer a patient information sheet during a routine consultation. Acceptance of the patient information sheet is entirely voluntary. If patients take an information sheet, a member of the research team will subsequently contact them via telephone.

### 6.4 Informed consent

The patient's written informed consent must be obtained using the NMES trial Consent Form, which follows the Participant Information Sheet. The patient should be given a minimum of 24 hours after the initial invitation to participate before being asked to sign the Consent Form. Please note, only when written informed consent has been obtained from the patient can they be considered a trial participant.

## 7.0 Randomisation

Randomisation will be performed centrally by the WCTU. Randomisation can only be performed once the participant has signed the Consent Form. The randomisation form should be completed and the WCTU contacted on the following telephone number:

**WCTU Randomisation line:**  
**[name]**  
(Open Monday – Friday, 9am – 5pm)

*N.B. This telephone number is strictly for randomisation and should not be used for general queries.*

Participants will be randomised to a trial arm using a 2:1 allocation ratio using balanced blocks. At randomisation, the participant will be given a unique participant trial number. These details should be recorded on the NMES participant randomisation form and the top copy returned to the WCTU within four weeks.

After randomisation, the WCTU will fax confirmation to the Research Physiotherapist at the participating centre. Case Report Forms (CRFs) will contain the participant trial number, initials and date of birth. CRFs will also be sent to the Clinician, Data Manager or Research Nurse nominated as responsible for the participant. The participant's General Practitioner (GP) will be informed of the participant's randomisation, if the participant gives consent to do so.

It may be possible for participants to be recruited into other clinical trials, but this should be discussed with the WCTU.

## 8.0 Treatments

Participants will be allocated to receive one of the following treatment regimen(s):

### 8.1 Control arm

3–4 cycles of first line palliative chemotherapy administered as part of usual care by Nottingham University Hospital NHS Trust staff

### 8.2 NMES arm

3–4 cycles of first line palliative chemotherapy administered as part of usual care by Nottingham University Hospital NHS Trust staff and NMES programme.

#### NMES programme

NMES for 30min daily at home to the anterior thighs throughout chemotherapy. Because patients are generally anxious about starting chemotherapy we will defer initiating NMES until one week after commencing cycle one.

A physiotherapist will supervise the first session of NMES either at hospital or in the patient's home depending on patient preference. This will be supplemented by written instructions, weekly phone calls and home visits if required. When conducting home visits the physiotherapist will follow the WCTU home safety procedure SOP and a buddy system SOP.

Stimulation will be delivered using a MicroStim Exercise Stimulator MS2v2 (Odstock Medical Ltd, Wiltshire, UK) and self-adhesive electrodes placed over the body of the quadriceps. This is a CE marked (CE 02104) Class IIa Medical Device and the application is in accordance with the CE marking reference for the device.

The proportion of the treatment duration which is active, i.e. the stimulation phase of the duty cycle, will increase on a weekly basis from 11% to 18% to 25%, remaining constant thereafter.

The intensity or amplitude (device output 0–120mA, tested across 1000 $\Omega$ ) will initially be set to elicit a visible and comfortable muscle contraction.

Thereafter, patients will be encouraged to increase the amplitude as tolerated during the monitoring phone calls.

## 9.0 Trial assessments

### 9.1 Baseline assessments

- Quadriceps muscle strength: peak torque (Kg) measured using a portable Manual Muscle Tester dynamometer (Lafayette Instruments, USA).
- Toxicities
- Body composition: lean tissue mass of the body and thighs (kg) assessed by low-dose dual energy x-ray absorptiometry (DEXA) maximum dose per scan 37.4 $\mu$ Sv.  
The radiation dose for this procedure has been reviewed by a Medical Physics Expert and a Consultant Radiologist (page 3) and is considered to present 'trivial' and 'very low' risk.
- Physical activity level: mean daily step count assessed by an ActivPAL™ monitor over 1 week
- Nutritional intake: mean daily energy (kJ/d) and protein (g/d) intake estimated from a 3-day food and drink diary (2 weekdays, 1 weekend day)
- Fatigue: Multidimensional Fatigue Inventory
- Quality of life: the EORTC-C30 and LC-13.

### 9.2 Ongoing assessments during NMES

- Adherence to NMES: self-report daily diary of length of time NMES used and, if possible, an internal logger recording individual and total number of sessions used.
- Safety of NMES: toxicities and real-time adverse event reporting using CTCAE v3.0 criteria.

### 9.3 End of treatment assessments (9 weeks from start of chemotherapy)

- Quadriceps muscle strength
- Toxicities
- Body composition
- Physical activity level
- Nutritional intake
- Fatigue
- Quality of life
- *Response to chemotherapy*: overall objective clinical response categorised using Response Evaluation Criteria In Solid Tumours, documented from patients' medical reports.
- Experience of NMES - only in those that agree to participate in the qualitative sub-study and are not scheduled to proceed to 4 cycles of chemotherapy. A semi-structured interview exploring patients experiences of completing NMES during chemotherapy.

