### 9.4 End of treatment assessments for patients proceeding to cycle 4 (12 weeks from start of chemotherapy)

- *Response to chemotherapy*: overall objective clinical response categorised using Response Evaluation Criteria In Solid Tumours, documented from patients' medical reports.
- Experience of NMES - only in those that agree to participate in the qualitative sub-study and receive 4 cycles of chemotherapy. A semi-structured interview exploring patients experiences of completing NMES during chemotherapy.

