| NMES                  |                  |        |        |        |        |        |        |        |        |        |         |         |         |            |
| Daily application            |                  |        | X      | X      | X      | X      | X      | X      | X      | X      | X       | X       | X       |            |
| Supervision (home visit)     |                  |        | X      |        |        |        |        |        | X      |        |         |         |         |            |
| Supervision (telephone call) |                  |        |        | X      | X      | X      | X      | X      |        |        | X       | X       | X       |            |
| Adherence assessed           |                  |        |        |        |        |        |        |        |        | X      |         |         | X       |            |
| Interview (subgroup)         |                  |        |        |        |        |        |        |        |        | X      |         |         | X       |            |

*N.B. Serious Adverse Events (SAE) will be collected in real time via a designated SAE fax number.*

*Notes: the timing of assessments will be standardised to treatment cycles and thus will be sufficiently flexible to cope with delays during chemotherapy, e.g. due to neutropenia. The interview is completed either at week 9 or week 12 depending on the patient receiving 3 or 4 cycles of chemotherapy respectively.*

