### **11.3 Participant withdrawal**

In consenting to the trial, participants are consenting to NMES, trial follow up and data collection. If a participant wishes to withdraw from trial treatment, participating centres should nevertheless explain the importance of remaining on trial follow up for the purposes of data capture only. If the participant explicitly states their wish not to contribute further data to the trial, the WCTU should be informed. A completed withdrawal CRF should be faxed to the WCTU with the hard copy to follow soon after. Participants do not have to give a reason for their withdrawal but centres should make a reasonable attempt to find out why.

Participants should be withdrawn from the trial if they experience any of the following:

- Inability to tolerate electrodes and/or NMES
- Cessation of chemotherapy after 1 or 2 cycles

- Development of a complication that would preclude the use of NMES

Following withdrawal, no further clinical or non-clinical interventions or procedures would be carried out on the participant under the study protocol. No new samples or personal data would be collected. Data already collected in relation to the participant may be retained and used for the purposes for which consent has already been given, provided they are effectively anonymised and no longer identifiable to the research team or any other persons to whom access will be given.

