### 12.3 Sample size calculation

This trial is powered as a Fleming's single stage phase II trial of the intervention arm. The main endpoint is the proportion of patients completing a pre-determined level of compliance to the recommended NMES programme (NMES for 30min three times a week) measured using a self-report daily diary. Following advice from the cachexia subgroup of the NCRI Palliative Care Clinical Studies Group we have determined that 80% of patients should adhere to this minimum level in order to warrant a future phase III study. Conversely, if  $\leq 50\%$  adhered to this minimum level, this would give grounds to reject further study. Using a Fleming's one stage method, 20 patients will be required to distinguish between these rates (90% power,  $p=0.05$ ) and if  $\geq 15$  out of 20 patients adhere, this would warrant further investigation.

We have included a randomised control arm into this trial design in order to allow comparison of some secondary end points. Originally the trial started by randomising with a 1:1 allocation; however this was changed to a 2:1 in favour of the NMES arm allocation part way through the trial in order to support recruitment. As the study analysis is based on a within-intervention arm analysis, the statistical integrity of the study is not affected. A local audit suggests about 25% of patients drop out before reaching 3 cycles. We

require 20 patients in the treatment arm to be available for analysis; therefore we estimate that 26 patients need to be recruited to this arm. At the time of the change in the randomisation allocation ratio this meant that 47 patients would need to be recruited in total (26 to the treatment arm and 21 to the control arm).

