## **12.5 Statistical analyses**

A full statistical analysis plan will be developed before the first interim analysis of the trial data.

For the primary endpoint, the proportion (and 90% confidence interval) of patients completing NMES for 30min three times a week will be reported.

For the secondary (intention to treat) analyses, change in leg muscle strength from baseline will be compared between trial arms at 9, 17 and 20 weeks.

Descriptive statistics will then be presented for the following measures at 9, 17 and 20 weeks:

- Change in QoL score from baseline
- Change in body composition from baseline
- Change in nutritional intake from baseline
- Change in fatigue from baseline

Response to chemotherapy at 9 and 12 weeks will be described in each trial arm.

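### Tumour response is recorded only at week 9 or 12, while Section 11.3 withdraws early chemotherapy stoppers and bars new data, so early progression has no planned response category

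*Protocol*

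**What the plan says.** Section 9.3 lists response among the week-9 assessments: "overall objective clinical response categorised using Response Evaluation Criteria In Solid Tumours, documented from patients' medical reports". Section 9.4 repeats it at week 12, only for patients who proceed to cycle 4. The schedule in Section 9.6 marks response at those two points and nowhere else, and its notes add that "the timing of assessments will be standardised to treatment cycles".

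Section 11.3 gives reasons for which participants should be withdrawn from the trial. One is "Cessation of chemotherapy after 1 or 2 cycles". It then states: "Following withdrawal, no further clinical or non-clinical interventions or procedures would be carried out on the participant under the study protocol", and "No new samples or personal data would be collected".

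Section 12.2.2 lists response as a secondary outcome. Section 12.5 plans: "Response to chemotherapy at 9 and 12 weeks will be described in each trial arm". It names no denominator. Section 12.3 says: "A local audit suggests about 25% of patients drop out before reaching 3 cycles".

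Section 15.1 points the other way from Section 11.3. A participant whom the investigator moves to alternative treatment stays in the trial for follow-up and is analysed as allocated.

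**The concern.** Response to chemotherapy is first recorded at a time that a participant reaches only by staying on chemotherapy. Progression and death are plausible reasons for stopping after one or two cycles, and they are also the worst outcomes on the response scale. A participant who stops for either reason is withdrawn before the first response record is due, and the withdrawal text then prevents a later one. Selection into the response table is therefore tied to the outcome that the table describes.

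What is at stake is the description of disease control in each arm. Section 3.0 documents response as part of exploring why leg muscles weaken during chemotherapy, so an incomplete account of early progression weakens that description. The loss occurs at data collection, and an analysis plan written later cannot restore categories that were never recorded.

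**Working it through.** **Inputs from the protocol.** Drop-out before 3 cycles is about 25% (Section 12.3). Planned arm sizes are 26 NMES and 21 control, 47 in total, with 20 wanted for analysis in the NMES arm (Section 12.3).

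**The plan's own figure.** 20 / (1 − 0.25) = 26.7. The protocol states 26, and 26 × 0.75 = 19.5. The stated figure is reproduced to within one patient, so the 25% is the rate that the protocol itself plans on.

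**Participants without a planned response record.**
- NMES: 0.25 × 26 = 6.5
- Control: 0.25 × 21 = 5.25
- Total: 0.25 × 47 = 11.75, about 12, leaving about 35

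**Response rate, if the denominator is patients assessed and no early stopper responded (both assumptions).** Rate among assessed = all-randomised rate / (1 − 0.25) = 1.33 × all-randomised rate. In whole patients, with assumed numbers of responders:

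| Responders | Of 47 randomised | Of 35 assessed |
|---|---|---|
| 9 | 19.1% | 25.7% |
| 14 | 29.8% | 40.0% |
| 19 | 40.4% | 54.3% |

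If the denominator is all 47 and a missing record counts as non-response, the middle column is what is reported and there is no inflation.

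**Progression.** Let p be the share with progression among those assessed and f the share of early stoppers who progressed or died. The share over all randomised is 0.75p + 0.25f. Neither p nor f is in the protocol. With p = 30% (assumed):

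| f (assumed) | Progression or death, all randomised | Recorded, over assessed | Recorded, over all randomised (0.75 × 30%) |
|---|---|---|---|
| 25% | 28.75% | 30% | 22.5% |
| 50% | 35.0% | 30% | 22.5% |
| 75% | 41.25% | 30% | 22.5% |
| 100% | 47.5% | 30% | 22.5% |

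Over assessed patients, progression is understated when f exceeds p. Over all randomised, it is understated whenever f is above zero. In numbers, if half to all of the 12 progressed or died (assumption), 6 to 12 events are absent: 6/47 = 12.8% to 12/47 = 25.5% of those randomised.

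**The texts side by side.** Consider a participant whose chemotherapy is stopped in cycle 2 for progression and who is then given something else. Section 15.1 keeps this person in follow-up and analysis. Section 11.3 withdraws the same person and stops data collection. Sections 9.3 and 9.4 offer no response record before week 9. Following Section 11.3, the planned response category is blank.

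**The case against.** The strongest reply is that Section 12.5 does not say who is counted. A denominator and a not-evaluable category are ordinarily set in the analysis plan, which is not shown. This stands. A reader might infer that the protocol commits to an inflated response rate. It does not: the 1.33 factor is conditional on a denominator that the protocol never states.

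Second, some early failures do reach the database. Section 10.2 sends death or disability from progression to a CRF page. Section 11.3 lets data already collected be kept, asks centres to stress continued follow-up when a participant wishes to stop trial treatment, and asks for the reason for withdrawal. Section 15.1 favours retention. This also stands, so it would be wrong to say that nothing is known about these participants. But nothing links those records to a response category, and early progression without death or disability is not covered by Section 10.2.

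Third, early stoppers withdrawn under Section 11.3 have no week-9 strength measurement either. A reader might infer that the gap undermines the week-9 strength comparison. That is largely unsupported, because those who supply strength data at week 9 are scheduled for a response record at the same time.

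Fourth, two of the withdrawal reasons in Section 11.3 concern NMES itself and in practice arise only in the NMES arm. A reader might infer a biased comparison of response between arms. The protocol gives no rate for these withdrawals, and neither the size nor the direction of an effect on tumour response can be derived from it.

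**Conclusion.** The point holds in a limited form. The protocol ties response recording to reaching cycle 3 or 4, withdraws those who stop earlier, and bars new data on them, in conflict with Section 15.1. About 12 of 47 participants would have no planned response category on the protocol's own 25%. The part of these who progressed or died is unknown because the audit's reasons are not given. Under-recording of progression is likely; inflation of the response rate is only possible, and depends on the two assumptions shown. The matter is worth correcting because the gap arises at data collection. Its weight is modest: response is descriptive, carries no test or decision rule, and is absent from the outcome lists in Sections 1.0 and 2.0. The adherence endpoint and its decision rule are untouched.

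**What to change.** Start with Section 11.3, since changes to Sections 9.3 and 12.5 alone would ask for data that it forbids.

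- **Section 11.3:** separate data collection from the other consequences of withdrawal. State that stopping chemotherapy early does not end the capture of data from routine medical reports, unless the participant refuses further data use. The consequences for NMES and trial visits need not change for this purpose. Reconcile the text with Section 15.1.
- **Section 9.3:** for every randomised participant, record the reason for stopping and the response status when chemotherapy ends.
- **Section 12.5:** count documented progression or death from disease before week 9 as progressive disease. Show not evaluable, including other early deaths, as a separate category. Report by arm over all randomised participants.

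The cost is a few sentences in three sections, the reconciliation with Section 15.1, and one CRF line. No extra visit is needed, because response is already taken from medical reports. The reported response rate may be less favourable.

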### 9.4 End of treatment assessments for patients proceeding to cycle 4 (12 weeks from start of chemotherapy)

- *Response to chemotherapy*: overall objective clinical response categorised using Response Evaluation Criteria In Solid Tumours, documented from patients' medical reports.
- Experience of NMES - only in those that agree to participate in the qualitative sub-study and receive 4 cycles of chemotherapy. A semi-structured interview exploring patients experiences of completing NMES during chemotherapy.

### 9.5 Follow up assessments (17 / 20 weeks from start of chemotherapy)

- Quadriceps muscle strength
- Toxicities
- Body composition
- Physical activity level
- Nutritional intake
- Fatigue
- Quality of life.

A detailed assessment schedule is given in section 9.6 overleaf.

## 9.6 Schedule of trial

| Procedure / Assessment       | Trial time-point |        |        |        |        |        |        |        |        |        |         |         |         |            |
|------------------------------|------------------|--------|--------|--------|--------|--------|--------|--------|--------|--------|---------|---------|---------|------------|
|                              | Week -1          | Week 1 | Week 2 | Week 3 | Week 4 | Week 5 | Week 6 | Week 7 | Week 8 | Week 9 | Week 10 | Week 11 | Week 12 | Week 17/20 |
| Chemotherapy                 |                  | X      |        |        | X      |        |        | X      |        |        | X       |         |         |            |
| Response documented          |                  |        |        |        |        |        |        |        |        | X      |         |         | X       |            |
| Toxicities                   | X                |        | X      | X      | X      | X      | X      | X      |        | X      |         |         | X       | X          |
| Assessments           |                  |        |        |        |        |        |        |        |        |        |         |         |         |            |
| Leg muscle strength          | X                |        |        |        |        |        |        |        |        | X      |         |         |         | X          |
| Physical activity level      | X                |        |        |        |        |        |        |        |        | X      |         |         |         | X          |
| Body composition             | X                |        |        |        |        |        |        |        |        | X      |         |         |         | X          |
| Nutritional status           | X                |        |        |        |        |        |        |        |        | X      |         |         |         | X          |
| Fatigue                      | X                |        |        |        |        |        |        |        |        | X      |         |         |         | X          |
| Quality of life              | X                |        |        |        |        |        |        |        |        | X      |         |         |         | X          |
|                              |                  |        |        |        |        |        |        |        |        |        |         |         |         |            |
| NMES                  |                  |        |        |        |        |        |        |        |        |        |         |         |         |            |
| Daily application            |                  |        | X      | X      | X      | X      | X      | X      | X      | X      | X       | X       | X       |            |
| Supervision (home visit)     |                  |        | X      |        |        |        |        |        | X      |        |         |         |         |            |
| Supervision (telephone call) |                  |        |        | X      | X      | X      | X      | X      |        |        | X       | X       | X       |            |
| Adherence assessed           |                  |        |        |        |        |        |        |        |        | X      |         |         | X       |            |
| Interview (subgroup)         |                  |        |        |        |        |        |        |        |        | X      |         |         | X       |            |

*N.B. Serious Adverse Events (SAE) will be collected in real time via a designated SAE fax number.*

*Notes: the timing of assessments will be standardised to treatment cycles and thus will be sufficiently flexible to cope with delays during chemotherapy, e.g. due to neutropenia. The interview is completed either at week 9 or week 12 depending on the patient receiving 3 or 4 cycles of chemotherapy respectively.*

